#### Exploratory outcome measures

Qualitative and quantitative data for faecal microorganisms and biomarkers will be collected at baseline and at the end of double-blind treatment period (week 8) in a subgroup of 20 participants using GI-MAP™ assay (Invivo Clinical Ltd, UK) (Additional file 3). Participants will be selected for stool testing by the randomisation program at four selected sites so that ten participants from each treatment group will be tested. Data will be compared between treatment groups at week 8. Week 8 data will also be compared to baseline in all participants. Depending on the findings, other analyses might be performed in this exploratory dataset.Qualitative and quantitative data for intestinal motility, fluid volume, gas content and physiology will be collected at baseline and at 4 weeks of open-label treatment period in a subgroup of 16 participants using magnetic resonance imaging (MRI; Additional file 4). MRI data will be analysed using GIQuant image processing software (Motilent Ltd, UK). Only participants recruited to the main study from the University Hospital of North Durham and Newcastle Upon Tyne Hospitals will be invited to take part in this assessment.

### Study procedures

Participants will attend four study visits and receive one to two follow-up calls from their local research team. The schedule of visits and procedures conducted at each visit are summarised in Fig. 2.

**Fig. 2 Fig2:**
[figure not shown]
SPIRIT figure

#### Screening visit (− 2 weeks)

Informed consent will be obtained before any trial-specific procedures take place. Eligibility will then be determined against all criteria except for the stool consistency and abdominal pain criteria, which will be determined over the next 2 weeks using an electronic diary or a paper diary (for participants unable or unwilling to use the electronic diary). In addition, if a participant is of childbearing potential, a pregnancy test should be conducted after the 2-week screening period if a participant is confirmed to be eligible. Any criteria related to medical history or medication use that cannot be confirmed from the participant’s medical records at screening due to these not being available to the research team, can be initially assessed based on participant-reported information. However, such eligibility criteria must be confirmed against the participant’s medical notes before the participant is randomised. Vital signs (pulse, blood pressure) should be taken and confirmed to be within the following ranges: systolic blood pressure 90–140 mmHg; diastolic blood pressure 50–90 mmHg; heart rate 50–105 beats per minute.

Demographic data and current medical conditions and concomitant medications should be recorded in the electronic case report form (eCRF).

If the participant passes all the screening steps above, they are asked to complete a daily diary for 14 days to record stool consistency and abdominal pain. Training on how to use the electronic diary will be provided. If a participant is not able or willing to use an electronic diary, they will receive a paper diary containing identical questions. The participants will be instructed not to use any antidiarrhoeal medication during the screening period.

If the participant fails screening due to lack of screening phase symptoms, they can be re-screened once if the investigator believes the level of symptoms during the initial screening period were atypical for them and that there is a likelihood of achieving symptom thresholds on a further attempt. Participants should not be informed of the detailed reason(s) for why they failed screening in order not to influence their responses if re-screened. There should be a minimum of 2 weeks from failing screening to re-screening. Participants can be enrolled into re-screening remotely with a phone call unless they need to be re-consented (i.e. if patient information has changed). Participants can also be re-screened once if their vital signs were outside accepted range at initial screening.

#### Baseline visit (week 0)

After the 14-day screening period, screening diary data will be reviewed to check eligibility against the diary-based eligibility criteria. If an electronic diary was used, the diary system will automatically evaluate eligibility. If a paper diary was used, the site investigators should enter the diary data in the electronic database to allow the system to evaluate eligibility. A negative pregnancy test must also be obtained from any female participants of childbearing potential. Participants whose eligibility is confirmed will complete study questionnaires (IBS-SSS, IBS-QOL, PHQ-12 SS, WPAI:IBS) and be randomised to blinded treatment. Participants will also receive a pack of paper questionnaires (IBS-SSS, IBS-QOL, PHQ-12 SS, WPAI:IBS) to complete at home during the treatment phase. In total, 20 study participants at selected research sites will be selected by the randomisation program for stool sample testing. A separate consent will be sought for the provision of stool samples. The selected participants who consent, will be provided with a stool sample kit and a pre-paid postage envelope to post the sample to the central laboratory where the samples will be analysed. Participants recruited to the main study from pre-selected sites will be invited to take part in MRI assessment. These participants will be provided with a separate MRI information sheet at baseline visit and will have the opportunity to discuss the assessment with the research team and ask any questions before deciding whether they wish to consent to MRI by signing a separate written informed consent form. If a participant decides not to consent to stool sample testing or MRI assessment, this will not affect their participation in the main study. Participants who consent to MRI will undergo two scans: at baseline (although not necessarily on the same day as the baseline visit) and 12 weeks later, i.e. after 4 weeks of open-label treatment. The scans will take place at Newcastle Upon Tyne Hospitals and will not last longer than 20 min involving structural and motility (cine) imaging.

#### Follow-up call (week 2)

The site research team will contact the participants to ensure that they are continuing in the study and discuss any potential issues with the diary, questionnaires or the study treatment. No data will be recorded on this call, except for any reported AEs or changes in medical history or medications.

#### Follow-up visit 1 (week 8)

Participants will complete study questionnaires (IBS-SSS, IBS-QOL, WPAI:IBS, PHQ-12 SS), and AEs and changes in medical history and medications will be reviewed. All participants will receive instructions on how to take Enterosgel® for the next 8 weeks (open label phase). Participants will also be provided with copies of the paper questionnaires for the next 8 weeks. Those participants selected for stool sample testing at baseline will receive a stool sample kit.

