#### Packaging, labelling and supply

Both the placebo and Enterosgel® dilutions for double-blind treatment phase are manufactured in accordance with Good Manufacturing Practice (GMP) by Bioline Products s.r.o. (CZ), packed into identical 90-ml tubes and labelled in accordance with Annex I of the European Council Directive 93/42/EEC concerning Medical Devices. All study treatment will be stored at a Medicines and Healthcare products Regulatory Agency (MHRA)-approved warehouse facility (Wasdell Group, UK). After each randomisation, the site research team will email a request form with a unique randomisation code to a dedicated email address, which can only be accessed by Sponsor’s (Enteromed Ltd, UK) unblinded study coordinators. A coordinator will check the randomisation code against a pre-generated randomisation code list to determine whether it corresponds to placebo or Enterosgel® and will then submit a shipment request to the warehouse through a secure online portal. Supplies will be dispatched for delivery directly to the study participants within two calendar days from receiving the request (next day delivery for orders submitted before 2 pm). The supplied treatment will be sufficient to cover the entire 8-week treatment phase even if the maximum dose is taken every day.

Open-label treatment will be provided in sachets containing 15 g Enterosgel® and labelled in accordance with regulatory requirements. After a participant has been entered into the open-label phase, the site research team will send a treatment request to the Sponsor who will submit a shipment request to the warehouse as described above.

Treatment use and compliance are monitored through the daily study diary where the patients are asked to record how many doses of study treatment they used each day. If they did not take any treatment on a given day, then the electronic diary would also ask to provide a reason. These data are monitored by the study team on a weekly basis and the site teams are contacted if any issues are identified. Participants are not required to return any empty or unused tubes or sachets. Should the participant run out of study treatment during the study, they can request additional supplies through their research site.

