#### Biological materials

Stool samples will be taken by the selected participants at home using a provided kit that includes a postage envelope for sending the sample to the central laboratory where the samples will be received within 6 days from collection and immediately stored at 4 °C upon arrival in the laboratory. Protein aliquots will be prepared within 24 h of receipt and stored at − 20 °C until testing within 3 days. All protein testing will be performed using standard enzyme-linked immunosorbent assay (ELISA) methodology. Nucleic acids will be isolated from samples within 1–2 business days after sample receipt and isolated nucleic acids will be immediately stored at − 80 °C until testing. Analysis reports will be uploaded by the laboratory onto a secure online portal accessible by the sponsor’s research team. Results will not be shared with the research sites or the study participants. The stool samples will be destroyed by the central laboratory after the samples have been analysed.

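### The second stool kit is handed out only at the week 8 visit and used later at home, so the end-of-blinded-phase sample is not secured before open-label Enterosgel can begin

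*Protocol article*

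**What the plan says.** Exploratory outcome measures sets the time point. Faecal microorganism and biomarker data "will be collected at baseline and at the end of double-blind treatment period (week 8) in a subgroup of 20 participants", with selection by the randomisation program "so that ten participants from each treatment group will be tested". The planned randomised contrast is "Data will be compared between treatment groups at week 8". Week 8 is also to be compared with baseline in everyone tested.

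The operational sections describe how the sample is obtained:

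- **Baseline visit (week 0):** selected participants who consent receive one kit.
- **Follow-up visit 1 (week 8):** "Those participants selected for stool sample testing at baseline will receive a stool sample kit". At the same visit, "All participants will receive instructions on how to take Enterosgel® for the next 8 weeks (open label phase".
- **Biological materials:** "Stool samples will be taken by the selected participants at home using a provided kit". The sample is then posted. The only limit at this step is that it reaches the laboratory no more than 6 days after collection.
- **Packaging, labelling and supply:** "After a participant has been entered into the open-label phase, the site research team will send a treatment request to the Sponsor". The shipment request follows the route described for blinded supplies, which are dispatched to the participant's home no later than two calendar days after the request, with next-day delivery for orders placed before 2 pm.

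**The concern.** The outcome is defined at the end of blinded treatment, but the means of collecting it reaches the participant only at the visit that closes that phase and moves everyone to open-label treatment. Collection therefore follows the visit, at a time the participant chooses. Nothing in the article requires it to come before the first open-label dose.

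The arms can be compared as randomised only while they are on different treatments. A placebo participant who samples after starting open-label product contributes an Enterosgel-exposed value to the placebo mean. That pulls the week 8 difference towards zero, so a null finding in a comparison of ten against ten would be harder to interpret. It would also bring active exposure into the placebo arm's change from baseline.

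**Working it through.** The stool subgroup has no power calculation to reproduce: it is 20 participants, 2 × 10. The main-trial sample size has no bearing on this point. The check is first the order of events, then the possible size of dilution.

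**Order of events after the week 8 visit**

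| Step | Earliest time | Latest time stated |
|---|---|---|
| Second kit in hand | At the visit | At the visit |
| Open-label product requested | After entry to the open-label phase | None |
| Open-label product dispatched | Next-day delivery is possible for orders before 2 pm | Two calendar days after the request |
| Sample collected at home | After the visit | None |
| Sample at the laboratory | After posting | 6 days after collection |

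Two things follow.

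1. The kit normally arrives before the product, so there is a window for a clean placebo sample.
2. The window can be as short as a day or a few days, and no stated rule makes the participant use it. The 6-day limit runs from collection, so it bounds transit and not the delay between visit and collection.

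**Possible dilution**

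Let δ be the true mean difference between arms at the end of blinded treatment, k the number of placebo samples (out of 10) taken on Enterosgel, and e the fraction of the full effect reached by then. The expected observed difference is

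δ × (1 − e × k/10).

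- e = 1, k = 1: δ × (1 − 0.1) = 0.90δ, a loss of 10%.
- e = 1, k = 3: δ × (1 − 0.3) = 0.70δ, a loss of 30%.
- e = 0.5, k = 1: δ × (1 − 0.05) = 0.95δ, a loss of 5%.
- k = 0: no loss.

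**Power, as illustration only**

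This assumes a two-sided 5% t-test, 10 per arm, 18 degrees of freedom, unit standard deviation held fixed and e = 1. The noncentrality is d(1 − k/10) × √(10/2). The standardised differences d are assumed; the article gives none.

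| Affected placebo samples k | d = 1.0 | d = 1.32 | d = 1.5 |
|---|---|---|---|
| 0 | 56.2% | 79.7% | 88.7% |
| 1 | 47.8% | 71.0% | 81.4% |
| 2 | 39.5% | 60.8% | 71.8% |
| 3 | 31.7% | 49.8% | 60.3% |

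The article supplies neither k, e nor d, so these figures show what could be lost, not what is lost.

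**The case against.** The strongest reply is that the week 8 visit hands over instructions, not product. Open-label Enterosgel is ordered afterwards and couriered, so the default sequence is kit first, product later. The time point is also fixed: a sample taken on open-label product would depart from the outcome definition rather than follow it. A collection instruction may stand in the full protocol, the kit leaflet or Additional file 3, none of which is shown, and an article may properly leave such detail to them. The sub-study is exploratory, with 20 participants.

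Most of this stands, and it limits the point. It does not remove it. The hand-out time is stated in the article, and a leaflet given at that visit cannot move collection to before it. The courier interval makes a clean sample possible without securing one.

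A reader might infer three stronger things that the article does not support.

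- **That the visit starts open-label Enterosgel and the contrast is contaminated.** The supply route points to a gap before product arrives, and nothing shows that any sample is affected.
- **That about half the contrast is lost.** That figure needs, for example, 3 of 10 placebo samples on Enterosgel and 2 of 10 Enterosgel samples with the effect gone: 1 − 0.3 − 0.2 = 0.5. The shares have no source, and the sum also assumes full onset and full loss of effect within days.
- **That Enterosgel participants are necessarily off treatment during the supply gap.** The blinded supply covers the maximum daily dose for all 8 weeks and unused tubes need not be returned, so some participants may still hold product. How quickly any effect fades is not given.

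**Conclusion.** The point holds as a weakness in a stated schedule. The outcome is placed at the end of blinded treatment, but the kit is supplied too late to guarantee a sample from that period. Cross-over of placebo samples to Enterosgel is possible, not shown.

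Its size is up to 10% of the expected mean difference per affected placebo sample. This rests on ten per arm with all samples obtained, and on a full effect at sampling; a slower onset makes it smaller. The bias from this route is towards no difference. It matters because this is the sub-study's only planned between-arm comparison, but its reach is limited to an exploratory outcome in 20 participants.

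**What to change.** 1. Supply the second kit shortly before the week 8 visit, with the instruction to collect at the end of blinded treatment and before any open-label product is taken. This concerns only when the sample is taken; the treatment schedule is unchanged.
2. Record the collection date. The diary already records daily treatment use, so the date of the first open-label dose can be read from it.
3. In both arms, limit the between-group week 8 comparison to samples collected before the first open-label dose, and report how many are excluded per arm. For participants already past week 8, this step alone can still be applied where the dates are known.

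The cost is earlier supply of 20 kits, one line of instruction and one recorded date, with no extra samples or visits. The downside is the possible loss of a few late samples from an already small comparison.

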#### Follow-up visit 2 (week 16)

Participants will complete study questionnaires (IBS-SSS, IBS-QOL, WPAI:IBS, PHQ-12 SS), and AEs and changes in medical history and medications will be reviewed. All participants will be asked the following question (replying (a) yes or (b) no): With regard to your IBS symptoms, compared with the way you felt before you started study treatment, have you, in the past 4 weeks, had adequate relief of your IBS symptoms? Those participants who respond yes will receive a follow-up phone call in 8 weeks. Those who respond no will receive no further follow-up from the research team and will complete the study at this visit.

#### Follow-up call (week 24)

The site research team will contact those participants who had received adequate relief from the open-label treatment for a brief follow-up interview (see “Follow-up visit 2 (week 16)” section above). Any AEs and changes in medical history and concomitant medications will be recorded.

### Sample size estimation

The sample size calculation was based on demonstrating superiority for the primary outcome, i.e. response to treatment, with 90% power at 5% significance level. Assuming a response rate of 20% in the placebo group and 35% in the active treatment group, 182 participants per treatment group are required. Assuming 15% drop-out rate, in total 430 participants will need to be enrolled. The response rate of 20% in the placebo group is based on previous studies [31, 32]. The sample size was calculated using a power calculator for binary outcome superiority trial (Sealed Envelope Ltd).

### Recruitment

The study will be conducted at approximately 30 primary and secondary care sites and private gastrointestinal clinics in England. GP surgeries acting as patient identification centres will also refer patients to participating research sites. Sites will identify potential participants opportunistically and through searches of their patient databases, waiting lists, case records and referrals. Some research sites will utilise advanced software (Clinithink Ltd, UK) to identify potentially eligible patients from their clinical databases. The study can be advertised at participating sites and in public with materials approved by the Research Ethics Committee and the Health Research Authority. The study has developed a dedicated website which enables the public to check if they may be eligible and locate the contact details of their closest participating site. Finally, the study will recruit through the ContactME IBS registry [33], which contacts potentially eligible patients with details of the study. All potentially eligible patients will be provided with a patient information sheet either when visiting the GP/hospital/clinic or by post or email. Patients should be allowed at least 24 h to consider the study information before they are consented into the study.

### Randomisation

Eligible participants will be randomised by a delegated member of the site research team to a double-blind treatment group (placebo or interventional) in a 1:1 ratio. Randomisation will be performed using a computer-based online randomisation tool (Sealed Envelope Ltd, UK). The randomisation algorithm is based on the minimisation method where treatment allocation is stratified by study centre.

### Blinding

Participants randomised to the control group will receive placebo for 8 weeks. Participants randomised to the interventional group will receive Enterosgel® pre-diluted in water for 8 weeks. Both the participants and the research teams will be blinded to the treatment allocation until the end of the study.

### Unblinding

Unblinding (code-break) should only be performed during the trial in a situation where information about the participant’s trial treatment is necessary in order to provide appropriate and optimal medical care. Requests for unblinding will first be reviewed by the principal investigator (PI) or sub-PI who evaluates the information and the importance of unblinding in the given circumstances. If they decide that unblinding is necessary to ensure appropriate medical care, an unblinding request form should be submitted through the eCRF system. Unblinded treatment allocation will then be sent to the person who requested the unblinding. In case of emergency unblinding, the PI will be responsible for deciding whether the participant should continue on trial treatment. Unblinded participants should be followed up according to the study protocol until the end of the study.

### Data management

#### Data capture

Data on IBS symptoms and treatment use will be collected using a study-specific diary, which will be available as an electronic version developed by Sealed Envelope Ltd (UK). The electronic diary can be completed online by following a link provided on daily email and text message notification. For participants who are not able or willing to use the electronic diary, a paper diary will be provided. Copies of the paper diary are also provided as a back-up to participants using the electronic diary. For double-blind and open-label diaries completed on paper, the Sponsor’s research team will complete data entry into the electronic diary database. Study data recorded on any other paper source documents (e.g. questionnaires) will be transferred by the site investigators to an eCRF developed by Sealed Envelope Ltd (UK). The eCRF will be accessible via Internet browser and will be password protected to ensure that only authorised site staff and research team members can enter the system to view, add or edit data according to their permissions. Source data will be available at the site to document the existence of the study participants and will include the original documents relating to the study (demographics, medical history, medication, informed consent forms, questionnaires).

